#### Adjuvant chemotherapy

Four weeks after the end of the CCRT, six cycles of adjuvant therapy will be performed. Each 28-day cycle will begin with a daily dose of 150 mg/m^2^ of TMZ administered in the experimental group and control group. Starting with the second cycle, the dose of TMZ can be increased to 200 mg/m^2^. TMZ dose will be reduced to 100 mg/m^2^ at a daily dose if any of the following conditions are presented: absolute white blood cell count < 1 × 10^9^/L, platelet counts < 50 × 10^9^/L, and non-hematological toxicity class III. Moreover, this product will be terminated if non-hematological toxicity class III reappears or class IV reappears after the dose is reduced.

Based on the administration of TMZ, the dose of LEV in the experimental group will be adjusted to 1500 mg each time, twice a day, continuous for 6 cycles. The dosage of LEV will be adjusted according to renal function as follows: (1) mild abnormalities (creatinine clearance rate 50–79 mL/min): 750 mg, twice a day; (2) moderate abnormalities (creatinine clearance rate 30–49 mL/min): 500 mg, twice daily; and (3) severe abnormalities (creatinine clearance rate < 30 mL/min): 250 mg, twice daily. Increasing or decreasing the dosage by 500 mg/time every 2–4 weeks, twice daily, is recommended. During treatment, patients in the control group will be given placebo tablets with the same dosage and appearance as LEV.

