##### Chemotherapy

During radiation therapy, TMZ will be administered orally to both groups at a dose of 75 mg/m^2^. A continuous use of this product would be permitted for 42 days if the non-hematological toxicity ≤ grade I (except for hair loss, nausea, and vomiting), according to the Common Toxicity Criteria (CTC) [21]. The product will be suspended if the following conditions are met: absolute white blood cell count ≥0.5 × 10^9^/L and < 1.5 × 10^9^/L, platelet count ≥10 × 10^9^/L and < 100 × 10^9^/L, and non-hematological toxicity class II. This product will be terminated if the following conditions occur: absolute white blood cell count < 0.5 × 10^9^/L, platelet counts < 10 × 10^9^/L, and non-hematological toxicity class III or IV.

In addition, patients in the experimental group will also receive LEV tablets for the same period of time. To prevent adverse reactions that may occur early in treatment [23], a lower dose will be administrated. The initial treatment dose is 500 mg twice daily for 42 days without any changes. During treatment, placebo tablets will be given to patients in the control group with the same dosage and appearance as LEV.

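### The adjuvant temozolomide rules give no dosing action for a first class IV non-hematological event and no stop for any blood count, and they do not agree with the concurrent-phase rules

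*Protocol article*

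**What the plan says.** All of the rules below are in the Interventions part of the protocol article.

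**Concurrent phase (section Chemotherapy, 75 mg/m² for up to 42 days).** There are two tiers. Suspension applies to white cells from 0.5 to below 1.5 × 10⁹/L, and to "platelet count ≥10 × 10^9^/L and < 100 × 10^9^/L, and non-hematological toxicity class II". The second tier, termination, applies when white cells fall under 0.5 × 10⁹/L, and to "platelet counts < 10 × 10^9^/L, and non-hematological toxicity class III or IV".

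**Adjuvant phase (section Adjuvant chemotherapy, six 28-day cycles).** The starting dose is 150 mg/m², with an increase to 200 mg/m² permitted from the second cycle. Any one of these triggers reduces it to 100 mg/m²: "absolute white blood cell count < 1 × 10^9^/L, platelet counts < 50 × 10^9^/L, and non-hematological toxicity class III". Termination follows in one sentence: "this product will be terminated if non-hematological toxicity class III reappears or class IV reappears after the dose is reduced". No suspension tier is given.

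**General provisions elsewhere.** Investigators may withdraw a participant for reasons they consider inappropriate (Recruitment and eligibility criteria). Severe adverse events permit emergency unblinding (Randomization and blinding). A data monitoring committee reviews safety data (Quality control). Events of grade 3 or above are reported promptly, and participants are to be treated appropriately (Reports of adverse events).

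**The concern.** A set of toxicity rules should give at least as much action for a more severe finding as for a milder one. The adjuvant section does not. Class III has a rule at first occurrence, while class IV appears only in the termination sentence, tied to a reappearance after a reduction. For blood counts, the adjuvant rules have one step, the reduction, and nothing beyond it, although the concurrent section treats the lowest counts as grounds for stopping.

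What is at stake is participant safety. A clinician following the adjuvant section finds no temozolomide instruction for the most severe non-hematological class at its first occurrence. For counts that would have ended the drug during radiotherapy, the instruction is to continue at 100 mg/m². If each case is settled ad hoc by the investigators, temozolomide exposure and the rate of adverse events of grade 3 or above, a secondary outcome, will depend partly on individual judgment.

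**Working it through.** The plan gives no figure to reproduce. The check applies each section's rules, as written, to the same findings.

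**Reading conventions.** The concurrent termination list is read as any one condition being enough. The adjuvant reduction list says explicitly that any one is enough. The word *reappears* is read both literally and as a slip for *appears*.

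| Finding (everything else normal) | Concurrent phase | Adjuvant phase, unreduced dose | Adjuvant phase, already at 100 mg/m² |
|---|---|---|---|
| First class III | terminate | reduce to 100 mg/m² | first event: no further rule; reappearing: terminate |
| First class IV | terminate | **no rule met** | literal: no rule met; read as *appears*: terminate |
| White cells 0.3 × 10⁹/L | terminate | reduce to 100 mg/m² | **no further rule** |
| Platelets 5 × 10⁹/L | terminate | reduce to 100 mg/m² | **no further rule** |
| White cells 0.8 × 10⁹/L | suspend | reduce to 100 mg/m² | no further rule |
| Platelets 40 × 10⁹/L | suspend | reduce to 100 mg/m² | no further rule |

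**Class IV.** The only non-hematological reduction trigger is in "platelet counts < 50 × 10^9^/L, and non-hematological toxicity class III". It cannot easily be read as class III or worse: the concurrent section names both classes when it means both, and the outcome and safety sections use a ≥ sign. The termination sentence names class IV but conditions it on a prior reduction. Replacing *reappears* with *appears* leaves that condition in place. A first class IV event at 150 or 200 mg/m² is therefore uncovered on either reading.

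**Blood counts.** White cells below 0.5 also lie below the adjuvant reduction threshold of 1, and platelets below 10 also lie below 50. Both therefore trigger the reduction and nothing more, because the termination sentence contains no count. The same counts in a patient already reduced have no further stated consequence.

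**Extent.** Concurrent phase: 6 weeks. Adjuvant phase: 6 × 28 days = 168 days = 24 weeks. With the 4-week interval, 6 + 4 + 24 = 34 weeks, which agrees with the stated treatment period. The affected rules govern 24 of the 6 + 24 = 30 treatment weeks, in both arms.

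**The case against.** **The phases may differ by design.** The concurrent phase adds daily radiotherapy and the adjuvant phase does not, so a difference in rules is not in itself an error. This stands, and it is why the fix allows the difference to be declared intended. It does not explain why, within the adjuvant section alone, class III has a first-event rule and class IV has none.

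**The concurrent list is joined by *and*.** If all its conditions had to hold together, the contrast between phases would weaken. That reading is unlikely, since the adjuvant section introduces a list of the same form as any-one. The class IV gap within the adjuvant section does not depend on it.

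**General provisions cover these cases.** A reader might infer that a patient with a first class IV event would simply stay on 150 to 200 mg/m². The documents do not support that as a prediction: investigators can withdraw the participant, severe events permit unblinding and are reported, and the committee reviews safety. None of these provisions, however, says what to do with temozolomide.

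**An article condenses the full protocol.** This disposes of a complaint about dosing days within the cycle, which the full protocol may give. It does not dispose of rules that the article states explicitly and that leave these cases open as stated.

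**Stronger readings that fail.**
- A reader might take "Each 28-day cycle will begin with a daily dose of 150 mg/m^2^ of TMZ" to contradict the later increase and reduction. The later sentences modify it, and Table 1 gives the adjuvant range as 100–200 mg/m². The wording is loose but not contradictory.
- A reader might compare 100 with 75 mg/m² and conclude that exposure is higher in the adjuvant phase. The 75 mg/m² is given continuously for up to 42 days, while the article does not state the adjuvant dosing days, so exposure cannot be compared.
- A reader might expect variation between sites or bias between arms. The trial is single-center, both arms share the same temozolomide rules, and participants and outcome assessors are blinded. No mechanism for an imbalance between arms is shown.

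**Conclusion.** The point holds in a limited form. The adjuvant section is inconsistent within itself, because a first class IV non-hematological event at unreduced dose has no temozolomide action while class III does. It also does not agree with the concurrent section: class IV, white cells below 0.5 and platelets below 10 × 10⁹/L terminate the drug there, whereas in the adjuvant phase these counts only reduce it and no count ever stops it.

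The class IV gap at unreduced dose and the absence of any count-based stop hold under both readings of *reappears*. The uncovered first class IV event in an already reduced patient holds only under the literal reading. The contrast with the concurrent phase assumes that any one listed condition is enough there. It is exact only for class IV and for counts below 0.5 or 10; counts above those limits but below the adjuvant reduction thresholds would suspend the drug, not terminate it, in the concurrent phase.

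This is a safety defect in stated rules. It does not affect randomization or the primary analysis, and no effect on the comparison between arms is claimed. Because it concerns the most severe toxicities over most of the treatment period, and costs only wording to correct, it should be corrected.

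**What to change.** Reconcile the Chemotherapy and Adjuvant chemotherapy sections. The adjuvant rules should state explicitly what happens to temozolomide for:

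1. a first class IV non-hematological event at unreduced dose;
2. blood counts in the range that terminates the drug in the concurrent phase;
3. hematological toxicity that recurs after the dose has been reduced.

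The termination sentence should also say whether class IV must have occurred before, or whether any class IV event after a reduction is meant. If the difference between phases is intended, the text should say so. The clinical team decides the actions; this review proposes none.

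The cost is protocol wording, with whatever amendment step the trial requires. No new assessments are needed, because blood tests are already weekly during treatment and adverse events are already graded.

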Studies have demonstrated that the combination of LEV and TMZ is emerging as an optimal approach for improving the survival of GBM patients after surgery. It is therefore essential to conduct a prospective randomized controlled trial (RCT) to evaluate the effectiveness of TMZ plus LEV compared with TMZ standard chemotherapy. Seventy-three patients were enrolled in a Korean study (NCT02815410) that evaluated the effectiveness of LEV in GBM treatment. No differences were found in survival as a result of LEV. LEV had no significant side effects or overdose symptoms in the study, even when patients received an increased dose of up to 2000 mg/day and other AEDs as well [19]. However, the study was limited by a single-arm study design with external and historical control. In China, there is no correlative, randomized, and controlled trial that has been conducted to investigate the effects of LEV for GBM. As a result, we decided to conduct an RCT to explore the therapeutic effect of LEV plus TMZ for GBM, and thus provide an available therapeutic option for the treatment of GBM. The primary objective of this RCT is to determine whether the combination of TMZ and LEV is superior to standard TMZ chemotherapy in prolonging the progression-free survival (PFS) of GBM patients after surgery. This trial will also evaluate the efficacy of new chemotherapy regimens in improving the overall survival (OS), objective response rate (ORR), and the Karnofsky Performance status scale (KPS).

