### Interventions

The patients will be allocated to either the experimental group or the control group based on a blocked randomization sequence generated by SPSS 11 software for windows. A total of 34 weeks’ worth of medications will be prescribed to each group (including an interval of 4 weeks). The trial protocol was developed in accordance with the latest clinical standard care for GBM [22]. The standard of treatment for GBM patients who are under the age of 70 and have the good physical ability after maximal surgical resection currently consists of chemotherapy and radiation therapy (RT). Therefore, the interventions will be conducted according to the current clinical practice guidelines. A chart showing the administration of interventions is shown in Table 1.

**Table 1 Tab1:** A chart showing drug administration regimens

Treatment		Groups	
		Experimental group	Control group
**CCRT (6 weeks)**	RT	2.0Gy once daily, 5 days per week	
	TMZ	A daily dose of 75 mg/m^2^	
	LEV	500 mg, twice daily	Placebo tablets
**Adjuvant chemotherapy (6 cycles)**	TMZ	A daily dose of 100–200 mg/m^2^	
	LEV	200–1500 mg, twice daily	Placebo tablets

*Abbreviations*: *1 cycle*, 28 days; *RT*, Radiation therapy, *CCRT* Concurrent chemoradiotherapy

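### The adjuvant levetiracetam dose is fixed at 1500 mg per intake for all six cycles, but the same section recommends 500-mg steps that fit neither that dose nor its renal table

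*Protocol article*

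**What the plan says.** All places are in the protocol article.

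- **Concurrent phase (Chemotherapy, under CCRT).** The dose is fixed: "The initial treatment dose is 500 mg twice daily for 42 days without any changes".
- **Interval.** The adjuvant phase follows a pause: "Four weeks after the end of the CCRT, six cycles of adjuvant therapy will be performed". Interventions counts that pause in the total: "A total of 34 weeks’ worth of medications will be prescribed to each group (including an interval of 4 weeks". No levetiracetam dose is given for these four weeks.
- **Adjuvant phase, main dose (Adjuvant chemotherapy).** "the dose of LEV in the experimental group will be adjusted to 1500 mg each time, twice a day, continuous for 6 cycles".
- **Adjuvant phase, renal table (same section).** Per intake, twice daily, the dose is 750 mg for clearance 50–79 mL/min and 500 mg for 30–49 mL/min. The lowest band reads "severe abnormalities (creatinine clearance rate < 30 mL/min): 250 mg, twice daily".
- **Adjuvant phase, step sentence (same section).** "Increasing or decreasing the dosage by 500 mg/time every 2–4 weeks, twice daily, is recommended".
- **Table 1.** The adjuvant levetiracetam range is 200 to 1500 mg twice daily.
- **Eligibility.** Creatinine clearance must be at least 80 mL/min at entry.
- **Placebo and adherence.** Placebo follows the levetiracetam dosage. Adherence is a pill count of tablets taken against tablets scheduled.

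**The concern.** The main dose and the step sentence stand in one section and lead to different prescriptions in the first adjuvant weeks. A prescriber who follows the first gives 3000 mg/day from week 11. One who follows the second gives 2000 or 1000 mg/day for the first 2–4 weeks. The article does not say what triggers a step, whether steps govern the move from the concurrent to the adjuvant dose, or whether they govern renal reductions.

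Three things depend on the answer:

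- **The experimental treatment.** Levetiracetam is the only component that differs between the arms. The dose behind the efficacy and grade 3 or higher toxicity results should be one that a reader can state.
- **The placebo schedule.** It mirrors levetiracetam, so it is equally unsettled.
- **The adherence measure.** The pill count needs a scheduled number of tablets, and more than one schedule can be read from the text.

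For a patient whose renal function falls during treatment, the conflict is also a safety matter, because the table and the step sentence can give very different doses.

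**Working it through.** **Inputs.** Concurrent dose 500 mg per intake for 42 days; adjuvant dose 1500 mg per intake; step 500 mg per intake every 2–4 weeks; two intakes per day; six cycles of 28 days; renal doses 750, 500 and 250 mg; Table 1 lower bound 200 mg.

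**Duration, as a check on the timeline.** 6 weeks + 4 weeks + 6 × 4 weeks = 34 weeks, which reproduces the stated total. The adjuvant phase is 6 × 28 = 168 days and starts in week 11.

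**Move to the adjuvant dose.** (1500 − 500) / 500 = 2 steps made at once. Counted from zero, if nothing is taken in the interval, it is 1500 / 500 = 3 steps.

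**Cumulative adjuvant levetiracetam.** Total = 2 × Σ(mg per intake × days), over 168 days.

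| Reading | Calculation | Total | Against direct |
|---|---|---|---|
| 1500 mg from the first day | 2 × 1500 × 168 | 504 g | – |
| 1000 mg for 2 weeks, then 1500 mg | 2 × (1000×14 + 1500×154) | 490 g | −2.8% |
| 1000 mg for 4 weeks, then 1500 mg | 2 × (1000×28 + 1500×140) | 476 g | −5.6% |
| 500, 1000, then 1500 mg, 2-week steps | 2 × (500×14 + 1000×14 + 1500×140) | 462 g | −8.3% |
| 500, 1000, then 1500 mg, 4-week steps | 2 × (500×28 + 1000×28 + 1500×112) | 420 g | −16.7% |

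The last two rows assume that levetiracetam is not taken in the four-week interval and restarts at 500 mg. The article implies such a break, since the concurrent course is 42 days and the next dose given is the adjuvant one, but does not state it.

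**Renal table against the step sentence.** Starting from 1500 mg:

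- to 750 mg: 750 / 500 = 1.5 steps
- to 500 mg: 1000 / 500 = 2 steps
- to 250 mg: 1250 / 500 = 2.5 steps

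Steps of 500 mg reach 1000, 500 and 0 only, so 750 and 250 mg cannot be reached. Below 30 mL/min the table gives 250 mg per intake, while a first step gives 1000 mg: 1000 / 250 = 4 times as much.

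**Table 1.** (1500 − 200) / 500 = 2.6 steps, and 200 mg is not a renal dose. The lowest dose in the text is 250 mg.

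**Pill count.** If tablets are of one strength, a patient who takes every tablet of the 4-week stepped restart takes 420 / 504 = 83% of the direct schedule. With a first step to 1000 mg for four weeks the ratio is 476 / 504 = 94%. Either patient is 100% compliant with the schedule actually followed.

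**The case against.** The strongest defence is that the step sentence is only a recommendation and describes how 1500 mg is reached. That does not remove the conflict. A rise made in steps within the adjuvant phase delays 1500 mg, while the main dose is set for all six cycles, and a recommendation leaves the choice to each prescriber. An intermediate dose during the four-week interval would satisfy both statements, but the article gives no dose there and Table 1 has no row for it.

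A second defence stands in part. The renal table assigns doses directly, and nothing says they must be reached in 500-mg steps. The renal conflict therefore arises only if the step sentence governs the table, which the text leaves open. It also affects only patients who decline from at least 80 mL/min at entry, and the article gives no estimate of how many. However, the mild band starts directly below the entry limit, so a small fall suffices to enter the table.

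Third, the exposure difference is modest. If the first adjuvant dose is simply one step above the concurrent dose, 3% to 6% of cumulative dose is lost. That is correct. The larger 8% to 17% needs the inferred drug-free interval.

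A reader might go further in several directions that the documents do not support:

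- **Stop at week 34.** The article gives the end of treatment but no rule for discontinuing levetiracetam, and does not tie the step sentence to it. There is no contradiction. A taper within the six cycles, which would lower exposure by up to 33%, appears nowhere in the text.
- **Renal dosing in the concurrent phase.** The renal table belongs to the adjuvant section and the fixed 500 mg to the concurrent one.
- **Tolerability evidence.** The Background reports an earlier study in which side effects were not significant, "even when patients received an increased dose of up to 2000 mg/day". This describes that study and sets no ceiling for the 3000 mg/day planned here.
- **A null result explained by under-dosing.** The article gives no relation between levetiracetam dose and progression-free survival. The randomised intention-to-treat comparison remains valid.

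**Conclusion.** The point holds as an internal contradiction on dosing in the adjuvant phase. The direct move from 500 to 1500 mg per intake, with 1500 mg for all six cycles, does not fit a recommended change of 500 mg every 2–4 weeks. The step sentence also does not fit the 750 and 250 mg renal doses, and Table 1's 200 mg matches no dose in the text.

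The main effect is on the early adjuvant weeks, where the daily dose can be 3000, 2000 or 1000 mg depending on the reading. Over the whole phase the loss against the direct reading is 3% to 6%, or 8% to 17% under the assumption of a drug-free interval and a restart at 500 mg. The fourfold renal difference is conditional on the step sentence governing the table and on clearance falling below 30 mL/min during treatment. It should be corrected, but it does not threaten the validity of the randomised comparison.

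**What to change.** Reconcile the Chemotherapy section under CCRT, the Adjuvant chemotherapy section and Table 1, so that only one levetiracetam and placebo schedule can be followed. The text should state:

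1. whether the 500-mg step applies to the move from the concurrent to the adjuvant dose, and what is taken during the four-week interval;
2. whether the step applies to renal reductions or these are made at once;
3. a Table 1 range that agrees with the doses in the text.

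Then derive the scheduled tablet count for the pill-count adherence measure from that schedule, with any permitted dose change reflected in the denominator. The sponsor's clinicians choose the rule; no dose is proposed here.

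The cost is a wording amendment with matching pharmacy and placebo instructions. No further patients or procedures are needed.

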#### Adherence and concomitant care

Treatment adherence will be monitored by the Pill Counting method: if a drug is scheduled for 100 tablets and 20 tablets have been returned, the compliance is 80%. The adherence of participants will be improved by improving communication and supervision and by providing medication guidance during weekly visits (testing CBC, liver, and kidney function weekly).

Due to surgical trauma and tumor tissue, patients with glioma often have epileptic seizures. To control the occurrence of tumor-related epilepsy, antiepileptic drugs (AEDs) will be administrated in the clinic according to current clinical practice. The current clinical practice protocol includes the use of sodium valproate, the common first-line AED in patients with glioma [24, 25]. All of the medications used during the trial will be documented in a case report form (CRF).

The selection criteria and dose administration for antiepileptic use are as follows:
The patient suffered from epilepsy postoperatively, and/or epilepsy preoperatively: Patients will receive 20 mg/kg of sodium valproate once daily, and an EEG will be done 3 months later. The drug can be gradually reduced by 50 mg every 2 weeks if there are no obvious abnormalities.Patients without epilepsy before and after surgery: The patients will take 20 mg/kg of sodium valproate once daily for 2 weeks to prevent the occurrence of epilepsy, then the drugs will gradually be discontinued.Patients experiencing seizures during drug withdrawal: stopping withdrawal immediately and restoring the dosage to pre-seizure level.

